### Inclusion criteria

Patient-related:Subject (or their legal guardian) has read, understood and provided written informed consent, which has been reviewed and approved by the Institutional Review Board.At least 18 years of age.Male, infertile female, or female participants of child-bearing potential practicing an acceptable method of birth control with a negative pregnancy test within 7 days prior to study procedure.Projected life expectancy of greater than 2 years.The ability to comply with protocol follow-up requirements and required testing.

Clinical:Lifestyle-limiting claudication or critical limb ischemia (meeting angiographic entry criteria) affecting a lower extremity (Rutherford stages 2–5). Patients with Rutherford stage 2 are only eligible after unsuccessful conventional and/or medical therapy.Resting ankle-brachial index (ABI) ≤ 0.8 in the study limb.Inflow and/or outflow lesion (including the SFA orifice) - if present - has been treated successfully (treatment in same procedure permissible)

Angiographic and lesion requirements (assessed intraoperatively):TASC A-D lesions with stenoses and/or occlusions ≤ 32 cm (this allows max 2 × 17 cm stents with 1 cm overlap and 0.5 cm overstenting each end of lesion).Popliteal artery is patent 5 cm proximal to the radiographic knee joint line.Reference diameter of 4.0–7.0 mm in proximal and distal treatment segments within the SFA.Patent SFA orifice (the proximal 5 mm after femoral bifurcation).At least one patent (<50% stenotic) inflow vessel present, proven angiographically. Study eligibility is given when inflow lesion has been treated successfully (inflow treatment in same procedure permissible). Successful treatment of inflow lesion is defined as < 50% stenosis without death or severe vascular complication.At least one patent (< 50% stenotic) tibial artery runoff to the ankle present, proven angiographically. Study eligibility is given when runoff vessel lesion has been treated successfully (outflow treatment in same procedure permissible). Successful treatment of outflow lesion is defined as < 50% stenosis without death or severe vascular complication.Guidewire has successfully traversed lesion and is within the true lumen of the distal vessel.

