### Statistical analysis

Sample size calculation is based on the primary endpoint at 1 and 2 years represented by the percentage of in-stent neointima formation (relative to the stent diameter). Statistical significance between the groups will be tested using a *t* test at a level of significance of 0.05. To detect a difference of 0.8 standard deviations with a statistical power of 90%, a sample size of 34 patients in each group is required. With a maximum dropout rate of 15%, 40 patients will be randomized per group.

A two-sided *t* test will be used to compare amount of neointima between the two treatment groups. In case of non-normally distributed data, appropriate normalizing transformations will be applied. To evaluate the degree of association between the extent of chronic outward force (by using the data presented in Fig. 4 showing COF of stent fabricates according to stent diameter) and the amount of in-stent neointima, a linear regression analysis will be performed independently of the stent allocation group. Primarily, analysis will be based on intention-to-treat. If protocol deviations occur, the analysis will be performed both on an intention-to-treat and on a per protocol basis.

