A further advantage of CTA assessment of in-stent neointima is the option to locally compare different areas of COF (e.g., in places where some residual stenosis leads to higher compression of the stent and thus to higher chronic outward force, while in other regions where the stent is near its nominal diameter COF might be locally low). The stent diameter (and COF), as well as the amount of neointima, is known every 2 mm along the stent longitudinal access, therefore in-group and in-patient correlations of COF and neointima are possible in post hoc evaluations. If neointima formation is highest at the very same location as high COF, a direct activation of muscle cell proliferation may be assumed. Conversely, if neointima formation occurred downstream from areas with high COF, humoral or paracrine stimulations might be possible.

The study differs further from some similar previous trials in its generous inclusions criteria. Claudicants, patients with tissue loss, as well as diabetic patients are included; inflow and outflow lesion treatment is permissible, TASC A-D lesions are included. This was done in effort to perform the trial on a patient sample that closely represents real-world patients of a specialized endovascular center. The authors believe that it makes little sense to perform trials only on a highly selected collective of participants (representing possibly 1% of all patients) if then (as it is often the case) the conclusions drawn from such selective cohorts are then only generalized to the public anyway.

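### The primary comparison is a valid but unadjusted t test in a deliberately mixed population; prespecified adjustment for pre-randomisation vessel diameter would probably add precision at very little cost

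*Protocol article*

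**What the plan says.** The Statistical analysis section of the protocol article fixes the primary comparison: a two-sided t test "will be used to compare amount of neointima between the two treatment groups", "at a level of significance of 0.05", with normalising transformations if the data are not normal. No covariate is named. The linear regression in the same section relates chronic outward force to neointima without regard to arm, so it is not an adjusted treatment comparison.

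The sample size rests on the same test: "To detect a difference of 0.8 standard deviations" "with a statistical power of 90" per cent, "a sample size of 34 patients in each group is required". Then: "With a maximum dropout rate of 15%, 40 patients will be randomized per group".

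The population is wide. Inclusion criteria admit "TASC A-D lesions with stenoses and/or occlusions ≤ 32 cm", Rutherford stages 2 to 5 and reference diameters of 4.0 to 7.0 mm. The Discussion presents this breadth as intended: "Claudicants, patients with tissue loss, as well as diabetic patients are included". The Procedure section describes 1:1 block randomisation and states no stratification factor.

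**The concern.** The Discussion explains that a continuous endpoint was chosen to make the most of the study's power. A comparison of raw means then leaves in the error term any between-patient variation that baseline variables could explain. At about 34 patients per arm, a chance difference in vessel size between the arms also passes into the estimate unadjusted.

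Reference diameter is the natural candidate. It is checked intraoperatively for eligibility, so it exists before allocation. If it predicts percentage neointima, adjusting for it narrows the confidence interval with no additional patients. That matters most if the true difference is below 0.8 SD, a value for which the article gives no absolute difference or SD.

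**Working it through.** **1. Reproduce the stated design.** Inputs from Statistical analysis: two-sided alpha 0.05, difference d = 0.8 SD, power 90%, n = 34 per arm, dropout 15%. Power comes from the noncentral t distribution with df = 2n − 2 and noncentrality d·√(n/2).

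- n = 34: df = 66, noncentrality 0.8 × √17 = 3.298, power 90.15%.
- n = 33: power 89.3%, so 34 is the smallest sufficient number.
- Dropout: 34 / 0.85 = 40 per arm.

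Both stated figures reproduce exactly.

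**2. Is diameter plausibly prognostic on the document's own terms?** Both steps assume that the stent settles near vessel diameter.

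- *Endpoint.* In the CTA section, restenosis is (stent diameter − lumen diameter) / stent diameter. A 1 mm narrowing is 1/4 = 25% in a 4 mm stent and 1/7 = 14% in a 7 mm stent. Scaling by diameter removes the dependence only if narrowing is proportional to diameter, which the article does not say.
- *Oversizing.* Putting the LifeStent sizes in Table 1 into the oversizing formula in the Procedure section gives:

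| Vessel (mm) | LifeStent (mm) | LifeStent oversizing | LifeStent minus Pulsar (mm) |
|---|---|---|---|
| 4.0–4.5 | 6 | 25.0–33.3% | 2 |
| 4.6–5.5 | 6 | 8.3–23.3% | 1 |
| 5.6–6.5 | 7 | 7.1–20.0% | 1 |
| 6.6–7.0 | 8 | 12.5–17.5% | 1 |

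Under the trial's hypothesis that neointima rises with oversizing, diameter should therefore matter. Part of this is a treatment contrast that changes with diameter, that is, an interaction.

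**3. Size of the gain.** The documents give no R² for diameter or lesion length against the endpoint, so R² is an assumed range. With two covariates, the residual SD is SD × √(1 − R²), the effective difference is 0.8 / √(1 − R²), and df = 2n − 4 = 64.

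| Assumed R² | SE ratio | Power, n = 34 | Difference detectable at 90% (SD) | n per arm for 90% |
|---|---|---|---|---|
| 0 | 1.000 | 90.1% | 0.80 | 34 |
| 0.05 | 0.975 | 91.5% | 0.78 | 33 |
| 0.10 | 0.949 | 92.8% | 0.76 | 31 |
| 0.20 | 0.894 | 95.3% | 0.71 | 28 |
| 0.30 | 0.837 | 97.3% | 0.67 | 25 |

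If the true difference were 0.5 SD, power would be 53% unadjusted, and 57%, 62% and 68% at R² of 0.10, 0.20 and 0.30.

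**4. Cost.** The two degrees of freedom cost 90.15 − 90.12 = 0.03 percentage points. That figure treats the covariates as balanced between arms. Allowing for chance imbalance in two normal covariates with N = 68, the variance of the adjusted difference rises on average by (N − 3)/(N − 5) = 65/63 = 1.032. Power then becomes 89.2% at R² = 0 and 90.7%, 92.1%, 94.7% and 96.9% at R² of 0.05, 0.10, 0.20 and 0.30. The worst case is a loss of about 0.9 points, and the break-even R² is about 0.03.

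**5. Chance imbalance.** The standardised between-arm difference in a covariate has SD √(2/34) = 0.24. At its 95% limit (1.96 × 0.2425 = 0.475) and R² = 0.20, the unadjusted estimate shifts by √0.20 × 0.475 = 0.21 SD.

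**The case against.** The strongest reply is that nothing is broken. A two-sample t test is valid in a randomised trial, keeps its type I error and reaches the planned 90%. Covariate adjustment is often left to an analysis plan; neither that plan nor the full protocol in Additional file 1 is shown, and either could already add it. This stands as to seriousness. It does not remove the point, because the article names the primary test instead of leaving the model open.

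A reader might infer that precision is being thrown away. The documents do not support that: they report no R², SD or correlation, and at R² = 0 there is no gain. The endpoint is already scaled to stent diameter and taken over many levels along the stent, which may remove part of the variation.

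A reader might also infer that chance imbalance biases the result. It does not. Randomisation makes the imbalance random, and the t test's standard error already reflects it. The 0.21 SD shift is part of that random error, which adjustment would reduce.

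Three further limits stand:

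- Lesion length has weaker support. It appears only as an eligibility limit, the article does not say that it is recorded as a variable, and spot-stenting of several lesions leaves its definition open.
- The Procedure section describes landing-zone measurement after the randomisation step, so the covariate must be the eligibility measurement.
- The 2 mm versus 1 mm contrast in Table 1 is partly effect modification, which a main effect captures only in part.

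**Conclusion.** The point holds as an efficiency improvement, not as an error in the test, the type I error or the sample size. The stated 34 and 40 per arm are correct for the unadjusted test. Adjustment would move power at 0.8 SD from 90% to between 90.1% and 97.3% for R² between 0 and 0.30 (89.2% to 96.9% after allowing for average covariate imbalance). That range is assumed; the documents support the direction for vessel diameter and say nothing about its size. The support for diameter itself rests on the assumption that the stent settles near vessel diameter. Lesion length is a reasonable second covariate only if it was recorded before allocation.

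**What to change.** Before the 1-year data are analysed, replace the primary t test by a linear model for percentage neointima, on the transformed scale if a transformation is used. Include arm and the pre-randomisation reference diameter as a continuous covariate. State which eligibility measurement is meant (proximal, distal or their mean). Add total lesion length, with a definition that covers multiple lesions, only if it is recorded at eligibility. Keep the unadjusted t test as a supportive analysis.

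Do not adjust for implanted stent diameter or achieved oversizing. Both follow from allocation, and adjusting for them would remove part of the effect under study.

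The cost is a short addition to the analysis text and at most two degrees of freedom. Adjustment for diameter needs no new measurement, and the sample size stays as it is.

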**Methods:**

The BIOFLEX-COF trial is a prospective, quantitative, randomized study. Eighty subjects with symptomatic peripheral arterial lesions eligible for endovascular stent implantation will be enrolled and randomly assigned to either a high COF group (LifeStent Flexstar, Bard Peripheral Vascular Inc., Tempe, AZ, USA) or low COF group (Pulsar, Biotronik AG, Bülach, Switzerland) using an online randomization program to generate a random 1:1 group allocation (block randomization). After implantation and dilatation, COF at every 2 mm along the stent axis will be calculated from the actual stent diameter versus its nominal diameter.

There will be two follow-up evaluations at 12 and 24 months. Primary endpoint is the amount of in-stent neointima at 1 year, assessed by contrast-enhanced CT angiography (CTA). In the control examinations, stent diameter and true lumen diameter will be measured on DICOM images every 2 mm along the stent axis to quantify the relative amount of in-stent restenosis.

Secondary objectives are the amount of in-stent neointima at 2 years, device- and procedure-related adverse events and target lesion revascularization (TLR) rate.

The scheduled time for recruitment is 2 years. Recruitment is expected to be complete in October 2017.

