### Stent types

The low COF group receives a thin-strut stent (Pulsar, Biotronik AG, Bülach, Switzerland) with minimal oversizing (according to manufacturer’s instructions), the high COF group receives a stiffer stent (Lifestent Flexstar, Bard Peripheral Vascular Inc., Tempe, AZ, USA) with maximal oversizing (according to manufacturer’s instructions). The stent sizing is based on group allocation and SFA diameter measurements according to a sizing table (Table 1, showing the device sizing according to the vessel diameter). The Pulsar-18 is a laser-cut self-expanding nitinol stent loaded on a low-profile 4 F compatible over-the-wire coaxial delivery system. The stent has a flexible, thin-strut, open-cell design with helically aligned peak-to-valley crowns and six radiopaque markers at each end. It is completely covered with an amorphous silicon carbide coating.

**Table 1 Tab1:** Stent diameter used according to the vessel diameter

		Nominal stent diameter (mm)		
Vessel diameter (mm)	Pre-dilatation	LifeStent	Pulsar-18	Post-dilatation
4–4.5	3	6	4	4
4.6–5.5	4	6	5	5
5.6–6.5	5	7	6	6
6.6–7.0	6	8	7	7

The LifeStent Vascular Stent System is comprised of the LifeStent Vascular Stent (stents 20–80 mm) and the LifeStent XL Vascular Stent (stents 100–170 mm). The devices contain self-expanding, flexible, nitinol stents that expand to a preset diameter upon exposure to body temperature. The stents are equivalent to one another in design with only one difference located at the crown section; the LifeStent contain six tantalum radiopaque markers on both the distal and proximal ends of the stent, while the LifeStent XL stent does not have markers. Figure 4 shows the two stent types in detail.

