**Fig. 4 Fig4:**
[figure not shown]
Chronic outward force of different stent fabricates according to stent diameter

The two stent choices were based on bench test data provided by Biotronik AG on SFA stents from various manufacturers. Using these curves, the COF of each stent can be determined for every diameter below its nominal diameter. The LifeStent shows the steepest COF curve, while the AstronPulsar stent shows the flattest curve. When comparing both stents at a size of 6 × 100 mm the mean values for maximum and minimum RRF are lower for the Pulsar-18 compared to the LifeStent (0.464 and 0.413 N/mm^2^ vs. 1.160 and 1.059 N/mm^2^). Also mean values of maximum and minimum COF are lower for the Pulsar-18 compared to the LifeStent (0.313 and 0.249 N/mm^2^ vs. 0.732 and 0.575 N/mm^2^). The strut dimensions of the Pulsar-18 are 139 × 90 μm compared to 192 × 102 μm for the LifeStent.

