### Primary endpoint

Primary endpoint is the amount of in-stent neointima at 1 year, assessed by contrast-enhanced CT angiography (CTA). The volume of neointima inside the stent will be calculated by measuring every 2 mm along the longitudinal axis of the stent: (i) the diameter of the stent in two perpendicular directions and (ii) the diameter of the contrast-enhanced lumen in two perpendicular directions. The difference between these two measurements represents the thickness of the neointima, which will be represented relative to (as percentage of) the stent diameter.

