Approved closure devices may be utilized at the physician’s discretion. Clopidogrel 75 mg orally once a day will be given for a minimum for 3 months post-procedure. A loading dose of 300 mg will be given immediately after the procedure in patients who did not receive clopidogrel before. Aspirin 100 mg orally once a day will be administered through the study follow-up. In patients with oral anticoagulation aspirin will be the only antiplatelet drug required.

The diameter of implanted stents will be measured at every 2 mm along the stent axis on DICOM images of the respective completion angiography using image processing software (Image J, NIH, MD, USA). To compensate for distortion errors a calibration must be present on each image. By comparing the measured diameter with the nominal diameter of the stent the relative amount of oversizing will be calculated as:$$ \%\kern0.5em Oversizing\kern0.5em =\kern0.5em \frac{D_n-d}{D_n}\times 100 $$

(Dn = nominal stent diameter, d = actual stent diameter after implantation and post-dilatation)

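### The only planned regression on COF sets stent type aside, so a stent difference that does not act through COF can be reported as a COF association

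*Protocol article*

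**What the plan says.** The Statistical analysis section plans a two-sided t test between arms as the primary comparison. To assess how strongly COF and in-stent neointima are associated, it adds that "a linear regression analysis will be performed independently of the stent allocation group", with COF obtained "by using the data presented in Fig. 4 showing COF of stent fabricates according to stent diameter". The abstract (Methods) says that "COF at every 2 mm along the stent axis will be calculated from the actual stent diameter versus its nominal diameter". The Procedure section places that measurement at the end of the index procedure: "The diameter of implanted stents will be measured at every 2 mm along the stent axis on DICOM images of the respective completion angiography". The outcome is neointimal thickness, "which will be represented relative to (as percentage of) the stent diameter"; that diameter is taken on the follow-up CTA.

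The Stent types section shows that the devices differ in more than COF: "The strut dimensions of the Pulsar-18 are 139 × 90 μm compared to 192 × 102 μm for the LifeStent". Radial resistive force also differs (0.413–0.464 against 1.059–1.160 N/mm²), and of the Pulsar-18 it says "It is completely covered with an amorphous silicon carbide coating". The CTA section notes that blooming artifacts vary considerably between stents. Analysis of COF within an arm appears only in the Discussion: "in-group and in-patient correlations of COF and neointima are possible in post hoc evaluations".

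**The concern.** The t test compares two stents under two sizing rules. It cannot say whether a difference is due to COF or to another property of the device, so a statement about COF itself has to rest on the regression. If COF is nearly a label for stent type, a pooled slope without a stent term restates the arm difference in other units. A strut or imaging effect would then be read as a COF effect and carried into advice on stent type and size, which the abstract names as the purpose of the trial.

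The outcome scale adds a second route. Within one nominal stent size, a more compressed stent has a higher COF and also a smaller denominator in the percentage.

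**Working it through.** **The plan's own figure.** Normal approximation for 0.8 SD, 90% power, two-sided 0.05: 2 × (1.960 + 1.282)² / 0.8² = 32.8, so 33 per group. The noncentral t gives 33.83, so 34, and 34 / 0.85 = 40. The stated 34 and 40 reproduce. The article gives no operating figure for the regression.

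**How far COF is a label for stent type: bench values (Stent types, 6 × 100 mm).** Midpoints are (0.313 + 0.249)/2 = 0.281 and (0.732 + 0.575)/2 = 0.6535 N/mm², a difference of 0.3725 and a ratio of 2.3. With equal arms the between-arm variance is (0.3725/2)² = 0.0347. The documents give no within-arm SD, so a range is assumed (Pulsar/LifeStent):

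| Assumed SDs | Mean within-arm variance | Between-arm share |
|---|---|---|
| 0.02 / 0.045 | 0.0012 | 0.0347/0.0359 = 97% |
| 0.05 / 0.10 | 0.0063 | 0.0347/0.0409 = 85% |
| 0.10 / 0.20 | 0.0250 | 0.0347/0.0597 = 58% |

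**The same from Table 1.** If the stent takes the vessel diameter d, oversizing is (Dn − d)/Dn:

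| Vessel (mm) | LifeStent | Pulsar-18 |
|---|---|---|
| 4–4.5 | 25–33% | −12 to 0% |
| 4.6–5.5 | 8–23% | −10 to 8% |
| 5.6–6.5 | 7–20% | −8 to 7% |
| 6.6–7.0 | 12–18% | 0 to 6% |

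A simulation on this table (COF linear in oversizing, slope ratio 2.3, vessel diameter uniform on 4–7 mm, residual narrowing 0–15%) gave a COF–arm correlation of 0.89.

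**False positives from a non-COF stent effect.** Suppose COF has no effect and stent type shifts neointima by δ SD. The pooled correlation is then r = √share × (δ/2)/√(1 + δ²/4). With 68 patients, power is about Φ(atanh(r) × √65 − 1.96).

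- δ = 0.8, share 0.58: r = 0.762 × 0.371 = 0.283; 0.291 × 8.06 = 2.35; power 65%.
- δ = 0.3, share 0.97: r = 0.983 × 0.148 = 0.146; 0.147 × 8.06 = 1.18; power 22%.

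Simulation, 34 per arm, over the three SD pairs:

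| Non-COF shift | Pooled model | With stent-type term |
|---|---|---|
| 0.3 SD | 15–22% | about 5% |
| 0.4 SD | 24–35% | about 5% |
| 0.8 SD | 65–89% | about 5% |

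The Table 1 model, built differently, gave 19–21% at 0.3 SD, 43–44% at 0.5 SD and 81–82% at 0.8 SD, and 4–6% with a stent-type term.

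**The percentage outcome.** Take a 6 mm LifeStent with neointima 0.5 mm thick on each side, a 1.0 mm loss of diameter. In a 4.0 mm vessel, oversizing is 33% and neointima reads 1.0/4.0 = 25%. In a 5.5 mm vessel, oversizing is 8% and neointima reads 1.0/5.5 = 18%. The thickness is the same, but the higher-COF stent looks worse. In the Table 1 model, with thickness independent of COF and of stent type (nominal rate 5%):

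| Model | No re-expansion | 50% re-expansion by CTA |
|---|---|---|
| Pooled | 12–17% | 9–14%, mostly negative slopes |
| Stent term only | 30–56% | 9–15% |
| Stent term and stent diameter | 6–7% | 5–6% |

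A further run under Table 1 sizing gave 11–22% for the pooled model. If percentage neointima does not depend on diameter, every model stays near 5%.

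**The case against.** **The regression is only an association analysis.** It is neither the primary analysis nor a listed secondary objective, and the randomized t test does not need it. That stands, and it lowers the severity.

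**The confounding is an open design feature.** The Background contrasts a thin-strut stent with a thicker, stiffer one, and rewording the regression cannot separate those properties in the t test. That also stands. It is a reason to state the limit beside the pooled slope.

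**The wording may only mean that measured COF replaces assigned arm.** Stent type does enter through its COF curve. Even so, no stent term is stated, and the phrase points away from one. The supplementary full protocol, not shown here, may say more.

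**The adjusted slope is not a clean COF effect.** Conditioning on stent type gives up the randomized contrast. The Discussion says that local COF is high where residual stenosis compresses the stent, so plaque confounds the within-stent slope. Pulsar-18 has little oversizing, so the information comes mainly from LifeStent, where COF and diameter correlate at about −0.76. This stands: the adjusted slope belongs beside the pooled one and should not replace it.

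**Part of the evidence is thin.** The coating is described for Pulsar-18 only and the LifeStent's is not stated. The documented contrasts are strut size and radial resistive force; blooming is said to vary between stents in general, and the CTA section plans measures against it. The 0.8 SD row assigns the whole design effect to a non-COF cause and is an upper case.

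**A reader might infer that the ratio outcome by itself makes a false positive slope likely.** A simulation with 68 patients, diameter SD 0.6 mm and one COF curve gives 68%. The documents do not support that reading. COF is taken against nominal diameter, and Table 1 scales nominal size with the vessel. The two diameters also come from different examinations, so they share no measurement error.

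**Conclusion.** The concern holds, at the level of should-fix. The one planned analysis that uses COF itself sets stent type aside although COF is largely determined by it. False positives are about 15–22%, 24–35% and 65–89% for non-COF shifts of 0.3, 0.4 and 0.8 SD, against about 5% with a stent-type term. These rates rest on assumed within-arm COF SDs and 34 patients per arm; the COF curves (Fig. 4) are not shown.

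The outcome scale is a secondary and conditional problem: roughly 9–22% false slopes under Table 1 sizing, only if absolute thickness does not scale with diameter, with a sign that can reverse if the stent re-expands before CTA. A stent-type term alone does not remove it.

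Two stronger conclusions might be drawn and are not supported: that the primary result is compromised, since the t test does not depend on this regression, and that the adjusted slope is the causal effect of COF, since it is observational.

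**What to change.** In the Statistical analysis section, delete the qualifier that sets the allocation group aside and prespecify:

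- neointimal thickness in mm, (Ds − dl)/2, as the outcome of the COF regression;
- COF, stent type and reference vessel diameter as covariates, with a patient random effect if the 2 mm levels are the unit of analysis;
- this within-stent-type slope reported beside the pooled slope;
- a statement that neither the pooled slope nor the arm comparison can separate COF from other differences between the stents, and that the within-stent slope is observational.

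The cost is wording only, because the diameters are already measured every 2 mm. The price is a wider interval for the COF slope, with most of its information coming from the LifeStent arm. The change should be made before the outcome data are analysed by arm.
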